#### Primary outcome analysis

Linear regression models with robust SEs will be used to estimate the effect of the treatment groups on the CMDD-M score. The results will be reported as effect estimates. A sensitivity analysis of the primary outcome will be performed using a permutation-based Wilcoxon non-parametric test.

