### Settings

The study is conducted in two surgical wards and one geriatric ward at Uppsala University Hospital in Sweden. The surgical wards mainly handle emergency surgeries, as well as liver-pancreas, transplantation, oesophagus-stomach, endocrine and colorectal surgeries. The geriatric ward treats older patients with complex acute medical and rehabilitation needs. These two clinical specialties were selected to assess whether the intervention could have an effect across various clinical settings.

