### Control period (pre-intervention)

During the control period, care as usual will be provided at the study wards. Clinical pharmacists are part of the care team at the wards and primarily assist with medication reviews at patient admission and discharge but are not routinely involved in the discharge communication process. At hospital admission, medication reconciliation is conducted by either a pharmacist or a physician. If needed, a medication review is carried out by the physician, with or without support from a pharmacist. Any changes to the patients’ medication lists are made by wards physicians or nurse practitioners (specialised nurses at the surgical wards). Oral medication-related communication with the patient and/or informal caregiver is typically handled by nurses, physicians and pharmacists during patient consultations. At discharge, hospitals are required to provide a discharge summary to the next healthcare provider(s) and a discharge letter intended for the patient.^34 35^ Both documents are typically prepared by ward physicians and include details about the hospitalisation, medication changes (along with the rationales for those), planned treatment duration and follow-up plans. The discharge letter, however, is expected to be written in layman’s language. In some cases, these discharge documents are written by a physician who has not met the patient prior to discharge. Pharmacists sporadically assist in preparing these discharge documents, but not in a standardised manner. Additionally, it is standard practice for ward physicians to send specific referrals to the next healthcare provider(s), outlining follow-up requests related to medication changes. In addition, ward physicians conduct an oral discharge consultation, during which the patient is informed about the medication changes and follow-up plans before discharge.

While patients receive written information materials with practical information about the wards and surgical procedures at admission, no materials specifically address medications or medication communication at discharge. Inviting informal caregivers to participate in discharge consultations and HCPs conducting follow-up calls after discharge occurs in selected cases but is not routine practice.

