#### Component 2: Preparation of medication-related discharge documentation

Incompleteness and poor quality of medication-related discharge communication from hospitals is a common problem,^40 41^ making it difficult for subsequent HCPs to trust this information.^12 17 42^ Pharmacist involvement can significantly improve the completeness and quality of such communication.^40 41^ Consequently, in our study, the pharmacist will review relevant parts of the patient’s EHR and medication list prior to discharge to identify any lasting medication changes made during the hospitalisation. The pharmacist will collaborate with the discharging physician to reconcile follow-up plans for these changes. All medication changes, including reasons for the adjustments (when known), planned treatment duration, follow-up plans and the ward’s phone number for any post-discharge inquiries from the patient, will be documented in a standardised manner in the EHR by the pharmacist. This documentation will form the basis for detailing medication changes and follow-up plans in the patient’s discharge letter and the discharge summary intended for the next healthcare provider, both of which are written by a ward physician.

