### Sample size calculation

The sample size calculation is based on the primary outcome, which is the quality of medication-related discharge documentation measured using the CMDD-M. The intervention will be deemed successful if the average score is significantly higher in the intervention group compared with the control group. For the calculation, we assumed an evenly distributed sample between the two groups and set the target difference in CMDD-M scores at 1 point. This conservative target was chosen as it represents the smallest measurable step in the instrument. In practice, a 1-point difference may indicate the inclusion of medication changes in the discharge letter or discharge summary. Such an improvement reflects a critical enhancement in quality, with important implications for patient safety and continuity of care. Data from the pilot studies indicated that the baseline value for CMDD-M was 3.9 (SD 2.6) ([name], [name], [name], [name], *et al*: Facilitating patient empowerment at hospital discharge: A pilot study testing the feasibility of the IMPACT-care intervention, unpublished). Due to the maximum score limit in CMDD-M, the variance in scores is expected to differ between the control and intervention periods. This difference arises as scores may cluster near the upper limit, particularly in the intervention period where improved performance is anticipated, potentially leading to reduced variability compared with the control period. A two-sided t-test with Welch’s correction for df (to account for the variance difference between groups) was used. A power of 0.8 was considered sufficient to detect an increase, with a 5% two-sided significance level. Based on these assumptions, a sample size of 115 patients per group, for a total of 230 patients, is required.

Additionally, a permutation test using the Mann-Whitney U test was performed to assess the robustness of the t-test, yielding similar results.

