### Statistical analysis

A full statistical analysis plan will be finalised prior to any analyses. Statisticians from the Uppsala Clinical Research Center will oversee the statistical analyses. The primary analysis will follow the ITT principle, including all included patients in their assigned groups, regardless of protocol adherence. Additional analyses will include per-protocol analyses, that is, excluding patients with protocol violations.

Descriptive analyses of the study population will be performed, with continuous data presented as mean±SD for normally distributed variables or as median and range for non-normally distributed variables. Categorical variables will be reported as frequencies and percentages. All outcomes will be summarised by study group, overall and by ward, descriptively. Comparative statistics between study groups will be conducted, with all statistical tests being two-sided and a p value<0.05 considered statistically significant.

Models for analysing primary and secondary outcomes will include both unadjusted and fully adjusted analyses. Adjustments will account for age, gender, education level, ward type (geriatric or surgical), number of medication changes persisting post-discharge, number of medications at discharge, support by automatic dose-dispensation of medications and duration of hospitalisation. Effect estimates, including ORs, HRs and rate ratios will be presented with 95% CI and p values.

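### The sample size and primary model make no stated allowance for patients who share a discharging physician or ward pharmacist, and the adjusted model merges the two surgical wards

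*Protocol article*

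**What the plan says.** **Sample size.** Sample size calculation uses a two-sided Welch t-test "with a 5% two-sided significance level". It adds that "A power of 0.8 was considered sufficient to detect an increase" and says the authors "set the target difference in CMDD-M scores at 1 point". The pilot SD is 2.6 and the result is 115 patients per group. The only reason given for the Welch correction is unequal variance between periods. No ICC or design effect appears.

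**Primary model.** Primary outcome analysis says: "Linear regression models with robust SEs will be used to estimate the effect of the treatment groups on the CMDD-M score". The type of robust SE is not given. The sensitivity analysis is a permutation-based Wilcoxon test, described without physician or ward structure.

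**Who writes the scored documents.** Of the discharge summary and discharge letter, Control period says: "Both documents are typically prepared by ward physicians". Component 2 says of the same two documents: "both of which are written by a ward physician". It makes the pharmacist's note in the health record the basis for their medication content. Intervention period gives each ward one full-time-equivalent pharmacist, with experience that varies between pharmacists.

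**Wards.** Settings lists two surgical wards and one geriatric ward. Statistical analysis adjusts for ward type in two levels, so the surgical wards share one. The unadjusted model has no ward term. Study population and recruitment invites all eligible control patients, but ties intervention-period inclusion to pharmacist capacity, with random priority numbers generated at ward level.

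**The concern.** The primary outcome measures what staff write. A physician who writes full or sparse discharge notes probably does so for most patients, so scores from the same physician are likely to be correlated. In the intervention period, patients on a ward also share the pharmacist who prepares the text. In the control period pharmacists help only sporadically, so this source of correlation arises mainly in one period and does not cancel.

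If physicians contribute to one period only, an SE that assumes independence is too small: the CI is too narrow and the p-value too optimistic. The result on which the intervention is to be judged successful would then be less certain than reported. Ward coding is a question of bias rather than precision. If the two surgical wards differ in documentation and their shares of the sample change between periods, part of that difference enters the period effect, and a two-level term cannot remove it.

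**Working it through.** **Inputs from the protocol.** Two-sided alpha 0.05, power 0.80, difference 1 point, control SD 2.6, 1:1 allocation, n = 115 per group, three wards. The intervention SD is not stated, only expected to be possibly smaller.

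**Assumptions (no figures in the protocol).** m = patients per physician per period; ICC = correlation of scores within physician; degree of physician overlap between periods.

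**1. The plan's own figure.** With SD 2.6 in both periods, the normal approximation is n = 2(1.96 + 0.8416)² × 2.6² / 1² = 106.1, so 107. Exact Welch power gives 108. At n = 115, power under independence is 0.83. The stated 115 is therefore on the safe side, and at this SD it absorbs a design effect (DE) of 115/108 = 1.06.

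**2. Worst case: every physician in one period only.** DE = 1 + (m − 1) × ICC; effective n = 115/DE; true error of the naive test = 2[1 − Φ(1.96/√DE)].

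| m | ICC | DE | Effective n | Power, SD 2.6 | Type I error |
|---|---|---|---|---|---|
| 5 | 0.05 | 1.20 | 95.8 | 0.76 | 0.074 |
| 5 | 0.10 | 1.40 | 82.1 | 0.69 | 0.098 |
| 10 | 0.05 | 1.45 | 79.3 | 0.67 | 0.104 |
| 10 | 0.10 | 1.90 | 60.5 | 0.56 | 0.155 |

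Example, row 1: 1 + 4 × 0.05 = 1.20; 1.96/√1.20 = 1.789; two-sided tail 0.074. The power column is for a test with the correct SE. The naive test loses less apparent power only because its error rate is inflated: simulated with 23 physicians per period (5 patients each on average), no overlap and ICC 0.05, it rejects 80% of the time under a 1-point effect and 7.7% under no effect.

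**3. Same physicians in both periods, stable effects, balanced mix.** DE = 1 − ICC. For ICC 0.05 and 0.10, DE is 0.95 and 0.90, power 0.85 and 0.87 (0.846 and 0.865), and error 0.044 and 0.039. The naive SE is slightly too large.

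**4. Between the extremes.** Simulation of the naive test with 12 to 40 physicians per period and ICC 0.05-0.10 gives error rates of 0.064-0.160 with no overlap, 0.057-0.104 with 50% overlap and 0.048-0.051 with full overlap.

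**5. Ward-by-period changes, such as a pharmacist effect.** There are about 115/3 ≈ 38 patients per ward and period. DE = 1 + (m − 1) × ICC − m × CAC × ICC, where CAC is the correlation of a ward's effect across periods. With m = 38, ICC 0.05 and CAC 0.9 or 0.8: DE 1.14 or 1.33, power 0.78 or 0.71, error 0.066 or 0.089.

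**6. Smaller intervention SD.** At SD 2.4, 2.2 and 2.0 the required n is 100, 93 and 86, so 115 absorbs a DE of 1.15, 1.24 and 1.34. At SD 2.0, power is 0.90 under independence, 0.84 at DE 1.20 and 0.78 at DE 1.40. The error formula in step 2 does not contain the SD, so the inflation remains.

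**7. Ward term.** With two levels, bias in the period effect needs both a score difference between the surgical wards and a change in their mix. Capacity-limited inclusion makes the second possible; the protocol gives no figures on either.

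**The case against.** A reader might infer that the primary CI and the stated power are wrong. The documents do not support that.

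- No ICC, physician count or overlap is given, so clustering is plausible but not shown.
- The direction is not fixed. The same three wards supply both periods with about two months between them, so stable ward and physician effects largely cancel. The figures in step 2 assume complete turnover. The protocol expects some new staff during the intervention period, but nothing suggests full replacement.
- The SAP is still to be finalised and is not at hand; it may define the robust SEs as physician-clustered. On the analysis, the protocol is silent rather than in error.
- The margin of 1.06 applies only if both SDs are 2.6. The protocol expects less variability in the intervention period.
- The units are 230 patients with one score each. A score covers a letter, a summary and a follow-up request, which need not share an author, so a single author may not always exist.

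All of this stands and limits the point to a conditional one. It does not remove it: the completed power calculation has no allowance for shared staff, and the two-level ward term is a stated choice.

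A second tempting inference is that the plan must test whether the effect differs by ward type, since Settings says: "These two clinical specialties were selected to assess whether the intervention could have an effect across various clinical settings". That sentence explains the choice of sites. Aims and objectives sets no such objective and the trial is not sized for it. Statistical analysis states: "All outcomes will be summarised by study group, overall and by ward, descriptively". That is a defensible choice.

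**Conclusion.** The concern holds in conditional form. The 80% power and 5% error are valid if scores are independent or if the same staff contribute stably to both periods. Under the assumed worst case of 5 patients per physician nested in one period and ICC 0.05-0.10, power at SD 2.6 would be 0.76-0.69 and type I error 7-10%. With half the physicians shared, simulated error is about 6-10% over the assumed 12 to 40 physicians per period. With full overlap there is no inflation. A smaller intervention SD could recover most or all of the power at these design effects but not the error rate. Merging the surgical wards leaves avoidable confounding only if their scores differ and their mix shifts; its size cannot be computed from the protocol. Every clustering figure rests on assumed values of ICC, m and overlap.

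**What to change.** 1. In the adjusted models, replace ward type by ward with three fixed levels. The data are already held; the cost is one degree of freedom.
2. When the discharge documents are extracted, record a pseudonymised ID for the physician responsible for them, with a rule for cases with more than one author. The cost is one extra field from the health record.
3. For both CMDD-M outcomes (mean score and proportion at 9 points), report physician-clustered SEs with a small-sample correction, or a physician random intercept, at least as a sensitivity analysis. State in the SAP which type of robust SE the primary model uses. CIs may widen.
4. State that the power figure assumes independent patients, and report the number of physicians, patients per physician, overlap between periods and estimated ICC with the results.
5. Acknowledge that three wards are too few for ward-clustered SEs, so a change specific to one ward and period, including a pharmacist effect, stays a limitation that steps 1 to 3 do not remove.

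No period-by-ward-type interaction is needed for this point.

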#### Secondary outcome analysis

Logistic regression will be used to analyse the prevalence of patients achieving the maximum score (9 points) on the CMDD-M, with results presented as ORs. The PIMCH-Q score will be analysed using linear regression models, evaluating the three dimensions both separately and in total. Differences in the number of instances of non-adherence to medication changes persisting post-discharge will be assessed using quasi-Poisson regression models, with results reported as rate ratios. Logistic regression models will be used to analyse the prevalence of patients who are fully adherent to medication changes persisting post-discharge, with results reported as OR.

The difference in the prevalence of patients with unplanned hospital revisits, unplanned readmissions, emergency department visits and medication-related readmissions at 7, 30 and 90 days post-discharge will be compared with logistic regression models, with results presented as ORs. Time to first unplanned hospital revisit, time to first unplanned readmission and time to first emergency department visit will be analysed using Cox proportional hazards models. Patients who do not experience the event by the end of the study period or are lost to follow-up will be censored at their last known follow-up time, while patients who die before experiencing the event will be censored at the time of death. Results will be reported as HRs.

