## Introduction

 The ageing population is rapidly increasing, with individuals aged 65 and older expected to rise from 10% in 2022 to 16% by 2050.^1^ Older adults frequently experience multiple chronic conditions, making them two times as likely to require hospital care compared with younger adults.^2^ Medications are a primary treatment for many health conditions, and as the prevalence of multiple illnesses increases, so does the use of medications, increasing the risk of medication-related complications.^3 4^ One in six hospital admissions and one in five readmissions among older patients are medication-related,^5 6^ most of which are preventable.^7^ Care transitions, particularly hospital discharges, pose significant risks to patient safety and are highlighted by the World Health Organization as a focus for healthcare improvements.^8^ More than one-third of older patients experience adverse drug reactions within 8 weeks post-discharge,^9^ often attributed to poor communication and coordination between hospitals, subsequent healthcare providers and patients or their informal caregivers.^610^,^13^ Most hospitalised older patients experience changes to their medication regimens, which persist after discharge and should be effectively communicated to all individuals involved in their care.^14 15^

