Box 1The inclusion and exclusion criteria in the study. Patients meeting exclusion criteria 1–9 are excluded at the time of hospital admission, while those meeting exclusion criteria 10–15 are excluded at the time of dischargeInclusion criteria65 years or older. Manages their own medications, either independently or with support from an informal caregiver, prior to inclusion.Exclusion criteriaChecked at hospital admissionRegistered in a region outside the study hospital (limited data availability).Admitted from a nursing home (no own medication management prior to admission).Unable to receive information or provide consent independently (due to cognitive impairment or unresponsiveness).Already included in the study.Patient delocalised to the study ward with another medical discipline responsible for the patient’s care (formally, no study ward patient).In a late palliative phase prior to inclusion (intervention not suitable).Unable to communicate in Swedish (hindering intervention delivery).Has restricted personal information in the EHR (limited data availability).Admitted for transplantation (intervention not suitable).Checked at hospital dischargeDischarged to a nursing home (intervention not suitable).Patient transitions to late palliative phase during the hospitalisation (intervention not suitable).The patient is transferred to a non-study ward and is discharged from there (hindering intervention delivery).The patient dies during the course of the hospital stay (hindering intervention delivery).No medication changes that last post-discharge during the hospitalisation (intervention not suitable).The duration of stay on the study ward is less than 48 working hours (excluding time from 16:00 before weekends/public holiday to 08:00 the day after a weekend/public holiday) (hindering intervention delivery).EHR, electronic health records.

The researchers, who are employed by the hospital, screen the admission lists of the study wards daily on weekdays to identify eligible patients, who are then asked for inclusion by the researchers or clinical pharmacists on the ward. Eligibility is primarily determined through the patient’s electronic health records (EHR), with any uncertainties resolved through discussions with HCPs at the study wards. Once identified, patients are informed both verbally and in writing, and written informed consent (online supplemental material I) is requested. Patients meeting exclusion criteria 10–15 in box 1 are excluded at discharge.

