#### Demographic data

Demographic data collected from the EHR will include age, gender, renal function, admission and discharge dates, medication treatment at admission and discharge, whether the patient has support by automatic dose-dispensation of medications, disease diagnoses, primary diagnosis for admission, home care support, whether the patient lives alone and the number of emergency department visits and hospital admissions in the past year. Information about patients’ education level will be gathered through the researchers asking the patients at inclusion.

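### The single adjustment list leaves out the prior-year hospital use that the trial collects, so the revisit models cannot correct for it; day-7 medication-related readmission is too sparse for that list

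*Protocol article*

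**What the plan says.** Under Statistical analysis, the Protocol article applies both unadjusted and fully adjusted models to the primary and secondary outcomes and gives one covariate list: "Adjustments will account for age, gender, education level, ward type (geriatric or surgical), number of medication changes persisting post-discharge". The list continues with the number of medications at discharge, dose-dispensing support and length of stay. Neither version of the model is named as the main one.

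Under Secondary outcome analysis, the four binary healthcare-use outcomes "at 7, 30 and 90 days post-discharge will be compared with logistic regression models, with results presented as ORs". Time to first revisit, readmission and emergency visit is analysed by Cox regression. This section names no other covariate set.

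Under Demographic data, the trial collects "the number of emergency department visits and hospital admissions in the past year". That information does not appear in the adjustment list.

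The article gives no event rate for any healthcare-use outcome. The Introduction states, as background, that "one in five readmissions among older patients are medication-related".

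**The concern.** Earlier hospital use is the baseline version of the outcome itself, and it is a natural candidate predictor of a revisit. In a randomised trial, leaving it out would mainly cost precision. Here the control patients are recruited first and the intervention patients later, so covariate adjustment is the main protection against a shift in case mix. The exploratory interrupted time series does not help, because its list of outcomes does not include the healthcare-use outcomes. If the two cohorts differ in prior use, the difference carries through into every adjusted OR and HR for revisits, although the data to correct it are in hand.

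A second question follows from using the same list everywhere. A model with 9 or 10 slopes may be asked to run on very few events at day 7, most clearly for medication-related readmission.

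**Working it through.** **No plan figure to reproduce.** The article states no power or event count for these outcomes. Its one calculation, 115 per group, concerns CMDD-M. I take the total of 230 as given.

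**Step 1: the list against the data collected.** The list has eight covariates: age, gender, education, ward type, lasting medication changes, number of medications, dose-dispensing, length of stay. Prior-year emergency visits and admissions are collected and are not among them.

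**Step 2: what an imbalance would do (illustration on assumed figures).** Assume no intervention effect, a revisit risk of 25% in patients without prior use, and prior use in 45% of controls.

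- Prior-use OR 2: the odds without prior use are 0.25/0.75 = 0.333; doubled, 0.667, a risk of 0.40.
 - Controls: 0.45 × 0.40 + 0.55 × 0.25 = 0.3175.
 - Intervention at 35%: 0.35 × 0.40 + 0.65 × 0.25 = 0.3025. Group OR = (0.3025/0.6975)/(0.3175/0.6825) = 0.93.
 - Intervention at 30%: risk 0.295, group OR 0.90.
- Prior-use OR 3: the risk with prior use is 0.50.
 - Controls: 0.3625.
 - Intervention at 35%: 0.3375, group OR 0.90.
 - Intervention at 30%: 0.325, group OR 0.85 (0.84 if the risk without prior use is 15%).

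An imbalance in the other direction would move the OR above 1.

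**Step 3: bias against sampling error.** At a 25% event rate in each group of 115, SE(log OR) = √[2 × (1/28.75 + 1/86.25)] = 0.305, a 95% interval of about 0.55 to 1.8 around 1. The logs of 0.93 and 0.85 are −0.073 and −0.163, so the bias is about 0.24 to 0.53 of one SE.

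**Step 4: slopes and events at day 7.** Eight covariates plus group give 9 slopes, or 10 if education has three levels. The readmission rates are assumed; the last column takes one fifth of the events.

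| Day-7 readmission rate | Events in 230 | Events per slope (9) | Medication-related |
|---|---|---|---|
| 2% | 4.6 | 0.5 | 0.9 |
| 5% | 11.5 | 1.3 | 2.3 |
| 8% | 18.4 | 2.0 | 3.7 |
| 10% | 23.0 | 2.6 | 4.6 |

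Ten events per slope would need 90 events, a day-7 rate of 90/230 = 39%. With 0.9 expected medication-related events, the Poisson chance of none at all is exp(−0.92) = 0.40.

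**Step 5: does the model fit?** Simulations used 230 patients, 10 slopes and assumed covariate distributions.

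- Share of trials in which the full model has no finite maximum-likelihood solution (600 runs per rate, group OR 0.5): 96% at about 2 expected events, 83% at 5, 62% at 7, 30% at 12, 9% at 23.
- Share in which the group term itself diverges (null effect): about 45% at 2 events, 16% at 5, 4% at 7, none at 12 or more. A repeat run, counting an absolute log-OR above 8 as divergence, gave 41%, 13%, 7% and under 1%.

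Most failures therefore fall on a nuisance covariate. The reported group OR is in real danger only at about 5 events or fewer.

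**The case against.** The case against is substantial in four respects.

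**Size and standing.** These outcomes are secondary, and the article says that revisits would need an impractically large sample. An imbalance of the assumed size moves the estimate by no more than about half a standard error. The non-randomised design is listed as a limitation. All of this stands and limits the importance of the point. It does not explain why a collected baseline counterpart of the outcome is left off the list.

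**Is imbalance built in?** A reader might infer that the exclusion "Already included in the study" depletes the later cohort of repeat admitters. The documents do not support that as an established effect. The criterion applies in both periods, and depletion needs included controls to return to these wards and qualify again. To lower prior use from 45% to 35% in a cohort of 115 by this route takes at least (0.10 × 115)/0.55 = 21 returning controls, 18% of them. Reaching 30% takes (0.15 × 115)/0.55, about 31, or 27%. No return rate is given. It is a possible mechanism and probably a small one.

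**Are all day-7 outcomes nearly empty?** A reader might also infer this. At a 5% to 10% readmission rate there would be about 12 to 23 readmissions, and the composite revisit adds emergency visits. Few events can be asserted with fair confidence only for medication-related readmission, and even there on assumed rates.

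**Perfect CMDD-M score.** A reader might extend the sparse-data argument to this outcome because few controls may reach 9 points. The model pools both groups, and the article expects intervention scores near the upper limit, so the extension fails.

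Finally, unadjusted models and descriptive summaries are planned, and sparse-data methods are ordinary SAP content. An interpretable estimate will therefore exist even if an adjusted fit fails. The unadjusted models do nothing about prior use, however, and the covariate list is something the article itself has fixed.

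**Conclusion.** The concern holds in two limited parts.

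First, the adjustment list omits prior-year emergency visits and admissions although they are collected. The adjusted logistic and Cox results for healthcare use therefore cannot correct for a difference in prior use between the successive cohorts. The omission is plain from the text. Its effect is not known: the group ORs of 0.93 to 0.85 rest on assumed prevalences, an assumed prior-use OR and an assumed baseline risk, and the direction could be the reverse.

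Second, day-7 medication-related readmission is likely to have about 1 to 5 events, if 2% to 10% of patients are readmitted by then and the background one-in-five share applies. At those counts the adjusted OR would often not be estimable. For the other early outcomes the model is overloaded, but the group term would usually remain finite at 12 or more events.

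Nothing here touches the primary outcome. It is a modest, inexpensive improvement to secondary analyses.

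**What to change.** - Add prior-year emergency visits and prior-year admissions, for example each as log(1 + count), to the adjusted logistic and Cox models for revisits, readmissions, emergency visits and medication-related readmissions. Keep the existing covariates: dropping length of stay, number of changes or number of medications to save parameters would give up plausible confounders.
- Report day-7 medication-related readmission descriptively, or as an unadjusted risk difference with a confidence interval.
- Use Firth-penalised logistic regression for the other sparse early time points, and fix in the SAP, before any analysis, which these are. The two added terms make this more useful.

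No new data are needed, and the article says that the SAP is to be finalised before any analysis. The cost is a slightly different covariate set and method for these secondary outcomes than for the rest.
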